**Project summary**

Patients presenting with acute ST elevation myocardial (STEMI) infarct urgently need revascularization. Standard of care is establishing bloodflow through the coronary vessels using thrombus aspiration catheter, and securing the result by using a metallic drug eluting stent. New kinds of non-metallic bioresorbable scaffolds are now available. They have however challenges in structural strength.

We want to compare the new bioresorbable scaffold with traditional metallic stents in a prospective, randomized, non-blinded, multicenter study in 120 STEMI patients. We will use optical coherence tomography to evaluate the results after 12 months.

We also want to see if modern multislice computed tomography can give useful information in the follow-up of stented coronary arteries after 12 and 24 months.

We are also analyzing thrombus aspirates for markers for stent performance.

**1 Rationale and background information**

- 1. **Background and current standard of care**

In patients presenting with myocardial infarct with ST elevation, Primary percutaneous coronary intervention (PCI) is the preferred treatment (ESC guidelines recommendation I A). Stenting has I A recommendation, and preferably with drug eluting stents (DES) in patients who are likely to be compliant to dual antiplatelet therapy (DAPT) and are not at an increased bleeding risk (II A recommendation). Thrombus aspiration with specialized catheter has an equally strong II A recommendation[1]. Thrombus aspiration followed by direct stenting without any further balloon dilatation has been shown to give better 1 year survival[2-6].

- 1. **New stent platforms**

Metallic drug eluting stents are being challenged by new stents made from biodegradable platforms, or BVS (Biodegradable Vascular Scaffold). The Absorb BVS (Abbott Vascular, Santa Clara, CA) is the first of these being commercially available in Norway. The second-generation Absorb BVS is a balloon-expandable device consisting of a polymer backbone of poly-l-lactide (PLLA) coated with a thin layer of a 1:1 mixture of an amorphous matrix of poly-d, l-lactide (PDLLA) polymer and 100 μg/cm^2^ of the antiproliferative drug everolimus. Two platinum markers located at each Absorb BVS edge allow for accurate visualization of the radiolucent Absorb BVS during angiography or other imaging modalities. The PDLLA controls the release of everolimus, 80% of which is eluted within the first 30 days. Both PLLA and PDLLA are fully bioresorbable. The polymers are degraded via hydrolysis of the ester bonds, and the resulting lactate and its oligomers are quickly transformed to pyruvate and metabolized in the Krebs energy cycle. Small particles, less than 2 μm in diameter, have also been shown to be phagocytized and degraded by macrophages. According to preclinical studies, the time for complete bioresorption of the polymer backbone is 2 to 3 years It has been proven to be safe and non-inferior to metallic everolimus stents in the ABSORB II, kohort B trial [7, 8]. The bioresorbable scaffold has obvious advantages over metallic, as it will not hinder any future revascularization. However there are concerns regarding the strength of the scaffold. It is therefore recommended with more rigorous lesion preparation, using balloons for predilatation. Currently only one small study has been published studying specifically BVS in STEMI patients. This study is not randomized and does not address the issue of predilatation[9].

**1.2 Imaging OCT**

OCT (optical coherence tomography) is emerging as a useful diagnostic tool in the treatment of coronary disease. The prospects for use in plaque assessment, thrombus characterization, strut apposition, acute damage after stenting and no-reflow situations are promising for clinical use in the acute setting in the cath lab. Furthermore, OCT assessment of tissue coverage and restenotic tissue characterization are invaluable tools in follow up studies in patients with coronary stents. It also gives a detailed image of the surface and immediate sub intimal layers with details that exceeds intravascular ultrasound (IVUS) with about tenfold better resolution (10-15 µm vs. 100-200µm)[10, 11]. Consensus standards for the use of OCT gives at firm base to standardize further OCT based investigations[12]. OCT is thus a superior tool in evaluating percutaneous coronary interventions techniques[13, 14]. OCT will also emerge as a valuable clinical tool in the acute setting in the cath lab. Introduction of OCT to our lab through a study like this, will ensure that the operators at our lab master this tool and its interpretation[15].

- 1. **Imaging MSCT**

Multislice computed tomography (MCST) is a non-invasiv method of imaging coronary arteries. It is however currently not specific enough to evaluate arteries with previous coronary stent. By performing av MSCT at 12 months and 24 months follow up, we will both extend the follow up period by non-invasive method and by comparing to OCT and angiography, hopefully improve coronary diagnostics by MSCT imaging. The results will be published in substudy papers. Details are described in separate protocol.

- 1. **Thrombus analysis**

**Methods**.

Aspirate from aspiration catheter Export Advance (Medtronic) will be filtered through 40 µm filter basket before fixation  in 4% buffered formalin. Aspirate will be fixed in formalin for at least 24 hrs before shipment to Amsterdam Medical Center for further embedding in paraffin and to be cut in 5µm slices and stained with:

1. Haematoxylin and Eosin (HE)  and elastic  van Gieson (EvG) stains respectively[[16-18](#_ENREF_16)] for conventional histomorphological evaluation.
2. I mmunohistochemical staining with SMA-1 antibody (smooth muscle cells), ant CD31antibody (endothelial cells and platelets) and anti fibrin.

**Analysis of tissue sections**

1. Sample size: aspired materials  will be measured in the tissue sections in mm2 morphometrically.
2. Histological compostion of aspirate: presence of thrombus material, plaque material or both in each aspirate will be recorded. Thrombus composition will evaluated semiquantitatively on presence and extent of erythrocyte content (HE), plateletcontent (CD31 immunostain), fibrin content (Fbrin immunostain), and granulocytes.
3. Thrombus age will be measured analytically according to previously published definitions of thrombus age:
4. Fresh (upto 1day): Composed of layered patterns of platelets, fibrin, erythrocytes and intact granulocytes.
5. Lytic thrombus (1-5 days): Characterized by areas of colliquation necrosis and/or karyorrhexis of granulocytes, presence of NET’s,
6. Organized thrombus (> 5 days): Ingrowth of smooth muscle cells, with or without depositions of connective tissue and capillary vessel ingrowth. (conventional-  and immunostains)

**Rationale**

The pathological analysis will be compared to pre-,post- PCI and follow-up OCT readings to establish if composition, size and age predicts residual thrombus pre PCI as measured stent result after PCI and primary and primary endpoint at follow-up as measured by OCT. These results will be published in a separate substudy paper.

- 1. **Study goals and objectives**

Study goal is to compare the performance of the Absorb bioresorbable scaffold with a metallic drug eltuting stent in the STEMI patient.

Hypothesis is that a bioresorbable vascular scaffold (BVS) is non-inferior to standard of care, eg. direct stenting with metallic DES, using direct stenting after thrombus aspiration.

**2.0 Study design**

The study is a prospective, randomized, controlled, non-blinded, multicenter study comparing metallic drug eluting stent with bioresorbable scaffold in STEMI patients. Primary endpoint Coronary Stent Healing Index, see 2.2.6 for definition.

**2.2 Patients**

We propose to include 120 patients presenting with STEMI with less than 12 hrs. history.

**2.2.1 Inclusion criteria are:**

1. History of chest pain < 12 hrs
2. ST elevation of ≥ 2 mm in ≥2 contigous precordial leads (V1-V6), and/or ≥ 1 mm in ≥ 2 contiguous standard leads (I, II, III, aVf, aVr,aVl).
3. Single vessel disease/ No other lesions expected to need recasularization
4. Clinical decision to treat with primary PCI
5. > 18 years
6. Oral informed consent

**2.2.3 Exclusion criteria:**

1. Contraindications to long term DAPT
2. Known kidney failure with GFR < 45
3. Cardiac arrest or severe cardiogenic shock (Persistent BP <90 mmHg, despite adequate treatment)
4. Other severe illness with life expectancy of less than 12 months (eg. malignancy, severe malnutrition, degenerative disease)

**2.2.4 Procedural contraindications:**

1. Heavy calcification, tortuous vessel or large side branch (> 2,5 mm) at culprit lesion.
2. TIMI 0-1 flow after aspiration
3. Unable to advance thrombus aspiration catheter

**2.2.5 Schedule of event registration**

Clinical events will be note at index procedure. Participants will be contacted by telephone after 3 and 6 months, and clinical control as outpatient at 12 months with MCST and echocardiography.

**2.2.6 Primary endpoint**

Coronary Stent Healing Index (cumulated):

1. Uncovered struts: 2% =1 – 5% =2 – 10% =3 - 15% =4 – 20% =5 – 25% =6 – 30% =7 – 35% =8 – 40% =9

2)    Uncovered struts in fornt of side branch on acquired or persistent malapposed struts. 10% =1 – 20% =2 – 30% =3 etc… til 100%=10

3)     Persistent malapposition: ≥2 nabo struts længde mindst 1 mm =1 ; ≥2mm=3 ; ≥3 mm = 3

4)     Acquired malapposition: ≥2 adjacent struts of at least 1 mm length  =2 ; ≥2mm=4 ; ≥3 mm = 6

5)     Neointimal thickness in one frame >200 =1 - >300 =2  - >400 =3 or diameter stenosis >50% =4 - > 75% =5

6)      Cumulated extra stent lumen increase in match cross sectional analysis: (gns. areal mål): ≥0.2mm2 =1 ; ≥0.4 mm2 = 2; ≥0.6mm2=3 ; ≥0.8 mm2 = 4 ;  ≥1.0 mm2=5 ; ≥1.2 mm2 = 6

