**3.3 Sample size calculation**

The Coronary Healing Score has not previously been validated in studies. The sample size calculation is therefore done using a Minimum flow Area (MinFA), the endpoint used in the TROFI trial, also investigating STEMI patients with OCT at follow up.

Following the assumptions of a Non-Inferiority design the sample size calculations of this study were based on pooled data of Cardialysis database from multiple trials in acute coronary syndrome where the MinFA was 4.95 + 1.39 mm2. The trial is powered for testing of noninferiority for the primary angiographic endpoint (Minimum Flow Area). In order to be able to reject the null hypothesis that standard treatment with DES produces a MinFA of at least 0.72mm2 better then the experimentaly treated group (BVS) requires a sample size of 54 patients per treatment group (alpha = 0.05 , power = 0.85 , predefined noninferiority margin = 0.72 mm2).

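### Item 3 of the primary endpoint's scoring key gives persistent malapposition of ≥2 mm and of ≥3 mm the same 3 points, so the ≥3 mm category has no effect

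*Protocol*

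**What the plan says.** Protocol section 2.0 names the endpoint: "Primary endpoint Coronary Stent Healing Index, see 2.2.6 for definition". Section 2.2.6 then lists six scored items, which are added together.

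- Item 1, uncovered struts, begins "Uncovered struts: 2% =1 – 5% =2 – 10% =3 - 15% =4 – 20% =5 – 25% =6" and continues in the same way to 9 points at 40%.
- Item 2, uncovered struts at a side branch or over malapposed struts: "10% =1 – 20% =2 – 30% =3 etc… til 100%=10".
- Item 3: "Persistent malapposition: ≥2 nabo struts længde mindst 1 mm =1 ; ≥2mm=3 ; ≥3 mm = 3". The Danish words mean adjacent struts over a length of at least 1 mm, which is the condition that item 4 gives in English.
- Item 4, acquired malapposition, uses the same three lengths (1, 2 and 3 mm) and gives 2, 4 and 6 points.
- Item 5: "Neointimal thickness in one frame >200 =1 - >300 =2 - >400 =3 or diameter stenosis >50% =4 - > 75% =5".
- Item 6, extra-stent lumen: "≥0.2mm2 =1 ; ≥0.4 mm2 = 2; ≥0.6mm2=3 ; ≥0.8 mm2 = 4 ; ≥1.0 mm2=5 ; ≥1.2 mm2 = 6".

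Section 2.2.8 refers back to 2.2.6 for the definition. Section 3.3 says of the index: "The Coronary Healing Score has not previously been validated in studies". No other section gives a second key for item 3 or a reason for the tie.

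**The concern.** A key that names a separate ≥3 mm category and gives it the points already earned at ≥2 mm contains a category that does nothing. Nothing in the protocol presents this as a deliberate ceiling, and the neighbouring items suggest a slip in one digit.

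The slip matters because of where it sits. The six items are summed, so an error in one enters the patient's primary-endpoint value directly. The index is unvalidated by the protocol's own account, and the protocol points to no published version that would settle the key. Section 4.2 says that the OCT core laboratory will know the treatment arm, because the two devices look different on the images. An evidently faulty key may be reinterpreted during reading, and here the readers can see which device they are scoring.

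**Working it through.** **Inputs.** The point values of the six items in section 2.2.6. For the sample size in section 3.3: SD 1.39 mm² ("MinFA was 4.95 + 1.39 mm2"), margin 0.72 mm², alpha 0.05, power 0.85, stated n of 54 per group.

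**Step 1: the plan's own figure.** With a true difference of zero and one-sided alpha of 0.05,

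n per group = 2 × (1.645 + 1.036)² × 1.39² / 0.72² = 2 × 7.19 × 1.932 / 0.518 ≈ 53.6, rounded up to 54.

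This matches the stated figure. It rests on minimum flow area and contains no quantity from the index, so no change to item 3 can alter it.

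**Step 2: point steps within each item.**

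| Item | Points | Steps | Maximum |
|---|---|---|---|
| 1 | 1 to 9 | all +1 | 9 |
| 2 | 1 to 10 | all +1 (reading the etc. as a continuation) | 10 |
| 3 | 1, 3, 3 | +2, 0 | 3 |
| 4 | 2, 4, 6 | +2, +2 | 6 |
| 5 | 1 to 5 | all +1 | 5 |
| 6 | 1 to 6 | all +1 | 6 |

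Item 3 alone has unequal steps, and it alone has a zero step. The listed maximum is 9 + 10 + 3 + 6 + 5 + 6 = 39.

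**Step 3: item 3 against the parallel item 4.**

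| Length | Item 3 | Item 4 | Half of item 4 |
|---|---|---|---|
| ≥1 mm | 1 | 2 | 1 |
| ≥2 mm | 3 | 4 | 2 |
| ≥3 mm | 3 | 6 | 3 |

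The only disagreement with half of item 4 is at ≥2 mm. Changing that one digit to 2 restores both the halving and equal steps of +1, the step used in items 1, 2, 5 and 6. The item maximum stays 3 and the listed total stays 39.

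**Step 4: size, if 1/2/3 is the intended key.** Only patients with 2 to <3 mm change, each by 3 − 2 = 1 point. If p₁ and p₂ are the arms' proportions in that band,

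shift in the between-arm mean = 1 × (p₁ − p₂).

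The protocol gives no malapposition frequencies, so the differences below are assumptions.

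| Assumed p₁ − p₂ | Shift (points) | Share of 39 |
|---|---|---|
| 0 | 0 | 0% |
| 0.05 | 0.05 | 0.1% |
| 0.10 | 0.10 | 0.3% |
| 0.20 | 0.20 | 0.5% |

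**The case against.** The strongest reply is that the right value is inferred. The protocol never states a 1/2/3 pattern or a two-to-one weighting of acquired over persistent malapposition. The ratio argument rests on two matching entries, one of which is itself a tied value. The top entry could be the slip instead. A key of 1/3/5, for example, also needs only one digit changed and also has equal steps. Under it the 2 to <3 mm patients would be scored correctly, and those at ≥3 mm would be 5 − 3 = 2 points too low. A deliberate ceiling of 3 points cannot be excluded either, although it would leave the ≥3 mm label pointless. Nor is the index regular in every respect: the cut-offs of item 1 are unevenly spaced at the start, and item 5 changes from thickness to stenosis partway. This objection stands against certainty about the value 2. It does not remove the inert category.

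A second reply is that the same key applies to both randomised arms, so the tie creates no expected difference unless the arms differ in the affected band. That stands. The devices differ physically, so equal frequencies cannot be taken for granted, but the documents do not show unequal ones.

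A reader might also infer that patients with 2 to <3 mm cannot be distinguished at all from worse patients. That holds only within item 3. Items 2 and 6 may separate them, and section 2.2.7.1 lists strut malapposition as a secondary OCT endpoint in its own right.

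**Conclusion.** The point holds in a limited form. As written, item 3 scores ≥2 mm and ≥3 mm alike, so its top category is inert, and this is unexplained and out of line with the other five items. That much needs no assumption. That 1/2/3 was intended is the most likely reading, not an established fact. The over-scoring of 1 point for patients at 2 to <3 mm, and the shift of 0.05 to 0.20 points in the between-arm mean, depend on that reading and on the assumed differences of 5 to 20 percentage points.

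A reader might go further and conclude that every such patient is certainly mis-scored, that the treatment comparison is biased, or that the design is underpowered as a result. The documents do not support this. They do not state the intended key, they give no malapposition frequencies by arm, and they give neither an SD nor a margin for the index against which a shift could be judged. The 54 per group does not depend on the index. The point is small in size but sits in the definition of the primary endpoint, and it should be settled before scoring.

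**What to change.** Compare item 3 in section 2.2.6 with the scoring sheet that the OCT core laboratory will use, and have the sponsor confirm the intended key. Then do one of the following:

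- if the intended key is the likely one, correct item 3 to ≥1 mm = 1, ≥2 mm = 2, ≥3 mm = 3;
- if two levels are meant, delete the redundant ≥3 mm category and leave ≥1 mm = 1, ≥2 mm = 3;
- if the sheet shows another key, print that key.

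Put the Danish words of the item into English in the same edit. Record the change as an amendment and lock the key before any 12-month OCT is scored, so that it cannot be settled by readers who know the arm. The cost is one digit or one deleted category, plus a check of one document. No sample-size work is needed.

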**2.2.7 Secondary endpoints**

**2.2.7.1**

OCT endpoints

1. Area stenosis
2. Lumen late loss
3. Crushed stent segments
4. Malapposition of stent struts
5. Minimum expansion of the stents expressed as absolute area and percentage of the closest reference area,
6. Vessel ostial stent area (acute and at FU)
7. Thrombus burden

**2.2.7.2**

Angiographic endpoints

1.TIMI flow pre and post PCI,

2.Blush grade

3.Thrombus burden

4. Angiographic complications

5. Contrast use

6. Procedure time

7. Radiation skin dose

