**2.3 Treatment step-by-step**

Before arrival et cath lab, loading with acetylic salisylic acid and one of the antiplatelet agents clopigrogel/pragusgrel/ticagrelor is mandatory. Heparin or bivalirudin at start of procedure. After angiography and confirmation of presence of thrombus GpIIb/IIIa inhibitors are administered at operators discretion.

After thrombus aspiration with TIMI flow 2 or more the patient will be asked to participate in the study. Oral consent witnessed by staff non-affiliated with the study will be obtained.

OCT scan will be performed after 0.2 mg intracoronary nitroglycerine for sizing and lesion evaluation. The patient is then randomized into one of two arms in a 1:1 distribution:

1. Direct stenting with everolimus eluting stent
2. Direct stenting with bioresorbable stent

Direct stenting is the preferred method of implantation to keep procedure as short and simple as possible. Predilatation will not considered protocol violation if deemed necessary by operator. After stenting and post dilation at operator’s discretion, a second OCT will be performed. Any further post dilatation will be performed at operator’s discretion. A final OCT will be done if further postdilatation is performed. 0.2 mg intracoronary nitroglycerine is administered before each OCT scan.

Patient will be asked to sign an informed consent after the procedure (<24 hrs).

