**3.2 Secondary endpoints and other variables**

Differences in categorical variables between the two groups will be analyzed using the chi-square test or Fisher´s exact test. Continuous variables will be analyzed using independent sample t-test and Mann-Whitney U-test, and time to event data will be analyzed using the Kaplan-Meier method and the log-rank test. OCT and angiographic parameters will be evaluated by Spearman correlation analysis. Binary logistic-regression analysis will be performed to identify independent predictors of difference in outcome. Pre and post PCI OCT of vessel size, lesion severity, lesion length. All p-values are two-sided. Level of significance is 5%. The analysis is performed on an intention to treat basis and by actual treatment.

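### Pre-PCI TIMI flow is listed as a secondary endpoint although it is fixed before randomisation, so a between-arm test of it cannot show a device effect (minor)

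*Protocol*

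**What the plan says.** Protocol section 2.2.7.2, under the secondary endpoints, opens the angiographic list with "TIMI flow pre and post PCI".

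Section 2.3 gives the order of events. Angiography and aspiration come first, then the invitation: "After thrombus aspiration with TIMI flow 2 or more the patient will be asked to participate in the study". Oral consent and a first OCT follow, and only then allocation: "The patient is then randomized into one of two arms in a 1:1 distribution". Stenting comes after that. Section 2.2.4 names "TIMI 0-1 flow after aspiration" as a procedural contraindication.

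Section 3.2 covers secondary endpoints and other variables together. It says "Differences in categorical variables between the two groups will be analyzed using the chi-square test" or Fisher's exact test, and adds "All p-values are two-sided. Level of significance is 5" per cent. It also plans a regression: "Binary logistic-regression analysis will be performed to identify independent predictors of difference in outcome". Candidate predictors are not listed, and no section names pre-PCI flow as a covariate.

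**The concern.** An endpoint should be something the allocated treatment could change. Flow before PCI is settled before either device is assigned, so neither device can influence it. Listing it as an endpoint and applying the general between-arm test puts a baseline comparison among the results. A chance imbalance could then be read as a finding for or against the scaffold.

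Post-PCI flow is the outcome that the device can affect. Section 3.2 compares it without reference to the grade recorded just before stenting, although that grade is needed anyway to establish eligibility.

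**Working it through.** **1. The plan's own figure.** Section 3.3 gives "alpha = 0.05 , power = 0.85 , predefined noninferiority margin = 0.72 mm2", an SD of 1.39 mm² and 54 patients per group. With a true difference of zero and alpha read as one-sided:

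n = 2 × 1.39² × (1.645 + 1.036)² / 0.72² = 3.8642 × 7.188 / 0.5184 = 53.6, rounded up to 54.

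This matches. A one-sided 0.025 gives 67 and does not. TIMI flow does not enter the formula, so nothing below changes it.

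**2. When each flow reading is taken**, in the order of section 2.3:

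| Reading | Relative to randomisation | Grades possible in enrolled patients |
|---|---|---|
| Initial angiogram, before aspiration | Before | No restriction stated |
| After aspiration, before stenting | Before | 2 or 3 only (section 2.2.4) |
| After PCI | After | No restriction stated |

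The protocol does not say which of the first two rows *pre PCI* means for TIMI flow. Both precede randomisation, so the conclusion is the same. The restriction to two grades applies to the second row only.

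**3. What the test can return.** With sound randomisation, the chance of each pre-PCI grade is the same in both arms, so the null hypothesis is true by design. For a two-category variable with share p in each arm and n patients per arm, the exact rejection rate is

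Σᵢ Σⱼ Bin(i; n, p) × Bin(j; n, p) × 1{test p-value ≤ 0.05}.

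Inputs: n = 54 (section 3.3) or n = 120/2 = 60 (section 2.2). The protocol gives no TIMI distribution, so p was assumed at 30%, 50% and 70%.

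| n per arm | p | Chi-square, uncorrected | Fisher |
|---|---|---|---|
| 54 | 30% or 70% | 4.95% | 3.05% |
| 54 | 50% | 4.35% | 2.72% |
| 60 | 30% or 70% | 5.25% | 3.08% |
| 60 | 50% | 5.48% | 3.53% |

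The false-positive rate is thus about the nominal 5% with chi-square and clearly below it with Fisher. A four-grade reading of the initial flow was not calculated.

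**4. What the extra test adds.** Section 2.2.7.2 has seven items, or eight tests if item 1 counts as two. Assume independent tests at 5% each and all nulls true. The chance of at least one false positive is then 1 − 0.95⁷ = 30.2% with seven and 1 − 0.95⁸ = 33.7% with eight. The pre-PCI comparison adds about 3.5 percentage points and no information about the device.

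**The case against.** - **A descriptive pair.** Item 1 may be meant as a before-and-after description, and section 3.2 is general wording that never says pre-PCI flow will be tested on its own. This reading is possible, but nothing in the text supports it: the item sits under endpoints and section 3.2 has no exemption.
- **Covariate use is lost.** A reader might infer that the listing rules out pre-PCI flow as a covariate. It does not. Recording it makes adjustment possible, and the regression in section 3.2 leaves its predictors open. The protocol does not prevent that use; it only fails to use the grade when comparing post-PCI flow.
- **Adjustment belongs in the SAP.** An unadjusted comparison of randomised arms is valid, and covariate choice is often left to an SAP. Both statements stand. Without a TIMI distribution the gain from adjustment cannot be quantified either, so it is a recommended improvement and not the correction of an invalid test.
- **Any significant difference is chance.** This is too absolute. The trial is open-label, and section 11.4 lets the investigator withdraw participants for ineligibility or protocol violation. Compromised allocation or selective withdrawal could also produce an imbalance. That would still not be a device effect.
- **Always a binary variable.** This is true only after aspiration; no section excludes grades 0 or 1 on the initial angiogram.
- **Thrombus burden has the same fault.** Section 2.2.7.2 gives no time of reading for it, so the documents do not support extending the point.

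**Conclusion.** The point holds as a minor one. Section 2.2.7.2 classes a variable fixed before allocation as an outcome, and section 3.2 as written tests it between the arms. If allocation is sound and all randomised patients are kept in their assigned arms, the test returns chance findings only, at 2.7% to 5.5% depending on test, arm size and assumed category share.

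The effect is confined to one item in a long, unranked list of secondary endpoints. The primary endpoint, the 54 per group and the power are unaffected. Section 6 states its expectations for minimal flow area, MACE and stent failure, not TIMI flow, so the protocol's main conclusions do not rest on this item.

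**What to change.** - In section 2.2.7.2, change item 1 to *TIMI flow post PCI*.
- Report pre-PCI flow as a baseline characteristic, with the initial and post-aspiration grades stated separately and no between-arm p-value.
- In section 3.2, compare post-PCI flow stratified by, or adjusted for, the post-aspiration grade (2 versus 3, the only grades eligible under section 2.2.4), instead of by the unadjusted chi-square or Fisher test alone.

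The cost is one line in each section, with no change to the sample size. Post-aspiration flow is already assessed for eligibility; the record only has to keep it apart from the initial grade. The drawback is small: strata may be sparse with 54 to 60 patients per arm, so an exact stratified test may be needed.
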